#### Secondary outcomes

Secondary outcome measures will include: (1) change in mean diastolic blood pressure at 12 months; (2) change from baseline in the proportion of overweight/obesity, smoking, alcohol intake, unhealthy dietary habits, and physical inactivity; (3) change from baseline in the proportion of individuals at high risk for CVD (10-year risk for CVD > 30%); (4) perceptions about quality and acceptability of CVD-specific interventions delivered by CHWs; and (5) CVD knowledge decay among CHWs at 12 months after training.

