### Sample size estimation

This will be a two-arm cluster randomized controlled trial using villages as units of randomization. The minimum sample size for the baseline cross-sectional survey is estimated according to the methods proposed in the WHO STEPwise approach to chronic disease risk factors surveillance (STEPS) [34]. The sample size is calculated for 95% confidence intervals (CI) (z = 1.96) on the basis of a 5% margin of error and an estimated prior population prevalence of hypertension of 25.9% from the nation-wide representative STEPS survey in Tanzania [35], a design effect of 1 and an anticipated attrition rate of 20%. Participants will be adults aged 25–64 years and categorized into four age groups for each sex, resulting in eight strata. The resulting sample size is 2950. Participants with elevated blood pressure during the baseline survey will be eligible and invited to participate in the intervention study.

The sample size for the intervention study is calculated to provide an 80% power to detect a ≥ 6.5 mmHg difference in mean SBP between the intervention and control villages at an alpha level of 5%, assuming an attrition rate of 20%, an inter-cluster correlation of 0.03, and a standard deviation (SD) of SBP of 15 mmHg. The resulting sample size is 258 participants per arm of six villages. Thus, the total sample size for intervention study will be 516 participants from 12 villages.

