Similar methods of DID will be used for the analysis of secondary outcomes including changes in mean DBP, changes in the proportion of other CVD risk factors, and changes in 10-year risk for CVD event. The 10-year risk for CVD event will be estimated using the Globorisk office charts [46] specific for Tanzania. The Globorisk office chart is a simple instrument which requires age, SBP, self-reported smoking status, and gender to predict one’s 10-year risk for CVD event. For participants in the intervention, changes in 10-year risk will be assessed by comparing the risk at baseline and end-line assessment.

Missing data and loss to follow-up are major issues of concern as they may compromise inferences of any trial. Efforts will be made during trial implementation to ensure complete follow-up and minimize missing data and loss to follow-up. During analysis, we will assess the magnitude and compare the baseline characteristics of participants lost to follow-up and those with end-line assessment data to see if there is any specific pattern of missing and loss to follow-up. Since there is no single universal method for handling missing data in trials [47], it is difficult to decide a priori the best way to handle missing data for this study. The decision to exclude missing data from final analysis or use multiple imputation analysis will be made after examining the magnitude and pattern of missing data. For all analyses, a two-sided *p* value of ≤ 0.05 will considered statistically significant.

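### Secondary outcome (3) is a proportion above a 30% risk cut-off, but the analysis section analyses 10-year CVD risk without the cut-off; one measure should be named, preferably mean individual risk

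*Protocol article*

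**What the plan says.** Under Secondary outcomes, item (3) of the protocol article is "change from baseline in the proportion of individuals at high risk for CVD (10-year risk for CVD > 30" per cent). That is a dichotomy: each participant is above the cut-off or not, and the arm-level summary is a proportion.

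Under Data analysis, Quantitative data, DID methods like those for the primary outcome are to be used for secondary outcomes, including "changes in the proportion of other CVD risk factors, and changes in 10-year risk for CVD event". A later sentence, which opens by referring to participants in the intervention, says that "changes in 10-year risk will be assessed by comparing the risk at baseline and end-line assessment". The 30% cut-off does not appear in the analysis section.

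The risk is read from an office-based chart, "which requires age, SBP, self-reported smoking status, and gender to predict one’s 10-year risk for CVD event".

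On the population, Sample size estimation says: "Participants will be adults aged 25–64 years and categorized into four age groups for each sex, resulting in eight strata". The trial cohort is a selected part of that sample: "Participants with elevated blood pressure during the baseline survey will be eligible and invited to participate in the intervention study". No expected distribution of 10-year risk is given, and the choice of 30% is not explained.

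**The concern.** The outcome list and the analysis section describe different quantities. A change in the proportion above 30% and a change in 10-year risk can give different answers from the same data. The analysis sentence uses the word proportion for the other risk factors and drops it for CVD risk, so on a plain reading the risk itself is analysed. With both descriptions in force, the choice between a threshold result and a continuous one can be made after the data are seen.

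The two candidates also differ in sensitivity. Of the four chart inputs, only SBP and smoking can respond to the intervention. A modest fall in risk counts towards the threshold measure only for a participant who starts just above 30%; every other change is ignored. A non-significant result on the proportion could then be read as no effect on CVD risk when the measure had little chance of showing one.

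**Working it through.** **1. The plan's own figure.** Inputs from Sample size estimation: difference 6.5 mmHg, SD 15 mmHg, ICC 0.03, six villages per arm, 80% power, alpha 5%, attrition 20%. With t quantiles on 2 × (6 − 1) = 10 df (2.228 and 0.879), the individually randomised size is 2 × [15 × (2.228 + 0.879)/6.5]² = 102.8 per arm. The fixed-cluster formula gives 102.8 × 0.97 × 6/(6 − 102.8 × 0.03) = 205.3. Allowing for attrition, 205.3/0.8 = 256.6, so 257 against the stated 258. The trial size for SBP reproduces and is not in question.

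**2. Effective size for the threshold outcome.** Analysed per arm: 258 × 0.8 = 206. Per village: 206/6 = 34.3. Design effect: 1 + (34.3 − 1) × 0.03 = 2.0. Effective number per arm: 206/2.0 = 103. The ICC is the one stated for SBP; none is given for this binary outcome.

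**3. Power to show a halving.** The share above 30% is assumed, because the documents do not give it. Effect size h = 2·arcsin√p₁ − 2·arcsin√p₂; power ≈ Φ(h√(n/2) − 1.96), two-sided 5%.

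| Assumed share | People per arm | Halved to | h | h√(103/2) | Power, n = 103 | Power ignoring clustering, n = 206 |
|---|---|---|---|---|---|---|
| 2% | 4 | 1% | 0.083 | 0.60 | 9% | 14% |
| 5% | 10 | 2.5% | 0.133 | 0.96 | 16% | 27% |
| 10% | 21 | 5% | 0.192 | 1.38 | 28% | 50% |
| 20% | 41 | 10% | 0.284 | 2.04 | 53% | 82% |

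With a t reference on 10 df, the clustered figures become about 8%, 14%, 24% and 45%.

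**4. Is a halving realistic?** This step is an illustration that uses two further assumptions from outside the documents: log-risk rises by 0.15 to 0.30 per 10 mmHg SBP, and log-risk is normal with SD 0.7 to 1.0. It ignores any change in smoking. A 6.5 mmHg fall then shifts log-risk by 0.65 × 0.15 = 0.0975 to 0.65 × 0.30 = 0.195, a relative fall of 9% to 18%. Only people starting between 30% and 0.30 × exp(0.0975) = 33% to 0.30 × exp(0.195) = 36% can drop below the cut-off. With n = 103 effective per arm:

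| Assumed share above 30% | Net number moved per arm | Power for the proportion |
|---|---|---|
| 1% | 0.5–1.1 | 4–7% |
| 5% | 1.9–4.7 | 5–13% |
| 10% | 3.3–8.4 | 6–19% |
| 20% | 5.4–14.1 | 7–26% |

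**5. The same shift on the continuous scale.** End-line log-risk compared between arms, without using the baseline values, has 10% to 52% power. Matching the assumptions pair by pair and taking the most favourable share (20%) for the threshold:

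- slope 0.15, SD 1.0: 7% for the proportion, 10% for the continuous measure;
- slope 0.15, SD 0.7: 10% and 17%;
- slope 0.30, SD 1.0: 16% and 29%;
- slope 0.30, SD 0.7: 26% and 52%.

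The continuous measure does better in every pairing, though it is not well powered on this cross-sectional calculation either.

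**6. Ageing.** Age is a chart input, and the same people are scored 12 months apart. A year of ageing raises scores in both arms, so subtracting the control-arm change removes most of it. It would remain in a before-after comparison within the intervention arm alone, which is one reading of the sentence containing "changes in 10-year risk will be assessed by comparing the risk at baseline and end-line assessment".

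**The case against.** The article is condensed, and "changes in 10-year risk for CVD event" may be shorthand for the proportion named in the outcome list. If so there is no mismatch. If instead it means the score itself, the continuous analysis is already planned and no information is lost. Either reading is possible, but the article does not settle which applies, and that is the defect.

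A reader might go further and infer that hardly anyone in a cohort aged 25 to 64 could be near 30%, so that a null result is almost assured. The documents do not support this. They give no risk distribution, the chart is not reproduced, and the cohort is selected for elevated blood pressure, which pushes scores up. At an assumed 10% above the cut-off, power for a halving is 28% with clustering and 50% without, which is low but not a foregone null.

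A reader might also infer that the threshold throws away the SBP effect. It does not: SBP is the continuous primary outcome and alone drives the sample size, and DBP is analysed as a mean.

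The power figures are only indicative. They compare end-line proportions, whereas the plan is a DID with baseline and end-line values on the same people, and the ICC is borrowed. Secondary outcomes need not be powered, and a high-risk proportion is a measure that policy readers recognise. All of this stands, and it limits the point to one secondary outcome without removing it.

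**Conclusion.** Secondary outcome (3) is defined as a proportion above 30% and analysed as a change in 10-year risk. The two passages should be reconciled; this conclusion rests on the text alone.

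That the threshold is the weaker choice rests on assumptions. With 2% to 20% above the cut-off, 206 analysed per arm and ICC 0.03, power for a halving runs from about 9% to 53%. For a 6.5 mmHg SBP effect, under the assumed slopes and spreads, it is at most about 26% with 1% to 20% above the cut-off. The actual share is unknown.

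Ageing is a minor matter under DID and a real one only for a within-arm comparison. The primary outcome, the sample size and the stated power are unaffected.

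**What to change.** In both Secondary outcomes and Quantitative data, name one measure: the between-arm DID difference in mean individual 10-year CVD risk at 12 months. Report the proportion above 30% descriptively by arm at baseline and end-line. Score both time points at the participant's baseline age, and say whether the sentence about participants in the intervention means a between-arm or a within-arm comparison.

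The inputs, the chart and the data collection stay as they are, so the cost is wording only. Trial status says that recruitment had not begun, so the change could be made before any data exist. The downside is that a difference in mean risk speaks less directly to policy readers than a high-risk proportion, which is why the proportion is kept as a descriptive result.

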#### Intervention process measures

The study also proposes to obtain and evaluate the following intervention process measures: (1) knowledge gain among CHWs following the training; (2) proportion of CHWs visits to study participants out of required visits per protocol; (3) proportion of participants with elevated blood pressure during the baseline survey who went to health facilities as per referral note; (4) proportion of participants with high blood pressure initiated on antihypertensive mediation; and (5) CVD knowledge gained by participants following the CHWs intervention.

### Sample size estimation

This will be a two-arm cluster randomized controlled trial using villages as units of randomization. The minimum sample size for the baseline cross-sectional survey is estimated according to the methods proposed in the WHO STEPwise approach to chronic disease risk factors surveillance (STEPS) [34]. The sample size is calculated for 95% confidence intervals (CI) (z = 1.96) on the basis of a 5% margin of error and an estimated prior population prevalence of hypertension of 25.9% from the nation-wide representative STEPS survey in Tanzania [35], a design effect of 1 and an anticipated attrition rate of 20%. Participants will be adults aged 25–64 years and categorized into four age groups for each sex, resulting in eight strata. The resulting sample size is 2950. Participants with elevated blood pressure during the baseline survey will be eligible and invited to participate in the intervention study.

The sample size for the intervention study is calculated to provide an 80% power to detect a ≥ 6.5 mmHg difference in mean SBP between the intervention and control villages at an alpha level of 5%, assuming an attrition rate of 20%, an inter-cluster correlation of 0.03, and a standard deviation (SD) of SBP of 15 mmHg. The resulting sample size is 258 participants per arm of six villages. Thus, the total sample size for intervention study will be 516 participants from 12 villages.

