### Sampling procedures

Participants for the baseline cross-sectional survey will be randomly selected from the intervention and control villages, using a multistage cluster random sampling technique. Lists of households in the selected study villages will be obtained from the village/sub-village leaders. From these lists, we will randomly draw a sample of households for each study village. At the level of household, a list of household members aged 25–64 years will be prepared. For households with more than one eligible participant, a simple random procedure using the next birthday rule will deployed to select an eligible respondent for interview.

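### The baseline survey is sized with a design effect of 1 although it samples 12 villages as clusters, so the 5-point margin behind 2950 is not met within the eight age-sex strata

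*Protocol article*

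**What the plan says.** Under "Sample size estimation" the protocol article sets out the baseline survey calculation: z = 1.96, "on the basis of a 5% margin of error", "an estimated prior population prevalence of hypertension of 25.9" per cent, and "a design effect of 1 and an anticipated attrition rate of 20" per cent. Participants are "categorized into four age groups for each sex, resulting in eight strata". It concludes: "The resulting sample size is 2950".

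Under "Sampling procedures" the same survey is drawn "using a multistage cluster random sampling technique". Households are taken at random from village lists, and one adult per household is chosen by next birthday. "Randomization and blinding" fixes the number of villages at 12.

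The second paragraph of "Sample size estimation" sizes the intervention study in those 12 villages with "an inter-cluster correlation of 0.03" and a standard deviation of 15 mmHg for systolic pressure.

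**The concern.** A design effect of 1 means that the survey is treated as having the variance of a simple random sample. The sampling section describes a cluster sample, and the paragraph that follows the survey calculation allows for village clustering of blood pressure in the same villages. One section therefore recognises village clustering for the trial and sets it to nothing for the survey. No reason for the value 1 is given.

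What is at stake is the precision claimed for the survey. Estimating prevalence and determinants of cardiovascular risk factors is a stated purpose of that survey (Abstract; "Trial design"). If the margin behind 2950 assumes independent respondents and equal strata, the design as described will deliver less than the calculation implies, mainly in the age-sex groups.

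**Working it through.** **Inputs.** All come from the protocol article: z = 1.96, p = 0.259, margin e = 0.05, design effect 1, attrition 20% and eight strata ("Sample size estimation"); 12 villages ("Randomization and blinding"); ICC 0.03, given for systolic pressure in the intervention study ("Sample size estimation"). Applying that ICC to hypertension status in the general adult survey is an assumption, so a range of 0.01 to 0.05 is shown.

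**Step 1: reproduce 2950.**
- n₀ = z²p(1 − p)/e² = 1.96² × 0.259 × 0.741 / 0.05² = 294.9, rounded up to 295.
- 295 × 1 (design effect) × 8 (strata) = 2360 responders.
- 2360 / (1 − 0.20) = 2950, exactly as stated.

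Without the factor of eight the answer would be 295 / 0.8 ≈ 369. The 5-point margin must therefore apply to each stratum, with 295 responders in each.

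**Step 2: margin within a stratum, allowing for villages.** With 295 responders spread evenly over 12 villages, m = 295/12 = 24.6. The design effect is DE = 1 + (m − 1) × ICC, and the margin is 1.96 × √[p(1 − p) × DE / 295].

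| ICC | DE | Margin per stratum |
|---|---|---|
| 0 (as planned) | 1 | 5.0 points |
| 0.01 | 1.24 | 5.6 points |
| 0.02 | 1.47 | 6.1 points |
| 0.03 | 1.71 | 6.5 points |
| 0.05 | 2.18 | 7.4 points |

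If all 2950 responded (m = 30.7), the margin at ICC 0.03 would still be about 6.2 points (DE 1.89).

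**Step 3: margin for overall prevalence.** With 2360 responders, m = 2360/12 = 196.7.

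| ICC | DE | Overall margin |
|---|---|---|
| 0.01 | 2.96 | 3.0 points |
| 0.03 | 6.87 | 4.6 points |
| 0.05 | 10.78 | 5.8 points |

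The overall margin equals 5 points when DE = 2360/295 = 8, that is, at ICC = (8 − 1)/(196.7 − 1) ≈ 0.036.

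**Step 4: can a larger sample restore 5 points per stratum?** With villages fixed at 12, m grows with the sample. Solving n = n₀[1 + (n/12 − 1) × ICC] gives n = n₀(1 − ICC)/(1 − n₀ × ICC/12). At ICC 0.03 this is 294.9 × 0.97 / (1 − 0.737) ≈ 1089 per stratum, and 1089 × 8 / 0.8 ≈ 10,890 people. At ICC 0.01 it is about 3870. At ICC 0.05 the denominator is negative, so no number of people in 12 villages would suffice.

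**Step 5: equal strata.** 2360 / 8 is exactly 295, so there is no slack. If one stratum has more than 295 responders, another has fewer. Random households with one adult by next birthday will reflect the age and sex make-up of the villages and of their households; nothing in that procedure equalises the eight groups.

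**The case against.** The strongest reply is that the article never says in words that the 5-point margin holds in each stratum. That is true: the margin and the strata are stated separately, and the outcomes and analysis sections name no stratum-specific estimate. A reader might speak of a promised stratum precision. The text supports only the weaker statement that 2950 cannot be reached any other way from the inputs given.

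It can also be said that multiplying by eight leaves ample room for clustering in the overall estimate. This stands at ICC 0.03, where the overall margin is 4.6 points, but not at 0.05. The ICC of 0.03 belongs to systolic pressure in people with raised pressure, not to hypertension status among all adults. This also stands, which is why the range is given; at 0.01 the per-stratum departure is small (5.6 against 5).

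Three stronger readings are tempting and should be resisted.
- A reader might infer that survey results will be reported with intervals that are too narrow. A planning design effect does not determine how variances are later computed, and this condensed article does not describe the analysis of the survey estimates.
- A reader might infer that particular age groups will fall far short of 295. The documents give no age distribution, and a full protocol may hold an age-sex allocation. What can be said is that the procedure as described does not ensure equal strata.
- A reader might infer that the trial itself is weakened. The primary comparison is sized separately, with an ICC. At 25.9%, 2360 to 2950 respondents would yield about 611 to 764 people (0.259 × 2360; 0.259 × 2950), above the 516 needed.

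**Conclusion.** The point holds as a mismatch between a planning input and the design, not as an arithmetic error: 2950 follows correctly from what was put in. A design effect of 1 is inconsistent with a multistage cluster sample of 12 villages and with the non-zero ICC used in the same section.

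At that ICC the per-stratum margin is about 6.5 points rather than 5, with a range of 5.6 to 7.4 over ICC 0.01 to 0.05. At the planned 2360 responders there is no reserve, so positive village clustering pushes the stratum margin above 5. The figures assume that an ICC for systolic pressure carries over to hypertension status, that the strata are equal, and that responders are spread evenly over villages. Unequal strata would widen the margin in the smaller groups by an amount that the documents do not allow one to calculate. The consequence is confined to the precision of a descriptive survey.

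**What to change.** In "Sample size estimation", keep 2950 and replace the design effect of 1 with a value consistent with village clustering, naming the ICC assumed for hypertension status. Restate the expected margins: about 6.5 points in an equal-sized age-sex stratum and about 4.6 points overall at ICC 0.03, each with the range for ICC 0.01 to 0.05 (5.6 to 7.4 and 3.0 to 5.8 points). Limit the 5-point precision to overall prevalence, and note that it holds up to an ICC of about 0.036.

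The cost is a change of wording and a less favourable stated precision. No participants are added; Step 4 shows why enlarging the sample within 12 villages would be a poor remedy. Under "Trial status" recruitment had not begun, so the change can be made before any survey data exist.

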### Sampling procedures

Participants for the baseline cross-sectional survey will be randomly selected from the intervention and control villages, using a multistage cluster random sampling technique. Lists of households in the selected study villages will be obtained from the village/sub-village leaders. From these lists, we will randomly draw a sample of households for each study village. At the level of household, a list of household members aged 25–64 years will be prepared. For households with more than one eligible participant, a simple random procedure using the next birthday rule will deployed to select an eligible respondent for interview.

### Randomization and blinding

The unit of randomization will be the village. A total of 12 villages (six from each district) will be randomly selected from the list of villages with active CHWs. The selected villages from each district will be grouped into two groups of three villages based on population size, type of health facility serving the village, and geographical distance between villages. One group of three villages from each district will be randomly assigned to intervention and another to control. This will ensure that intervention villages are bundled together but far away from control villages, hence minimizing contamination. The final randomization of intervention and control villages will be done by a statistician who is not involved in the implementation of field activities. Randomization of villages to the intervention and control arms will be done by a senior statistician based at Muhimbili University of Health and Allied Science in Dar es Salaam, Tanzania. Assignment of villages to either the intervention or control arm will be done after the baseline survey. Given the nature of the intervention, it is not possible to blind the CHWs who will be involved in the delivery of the intervention. The study design and flow chart are shown in Fig. 1. The SPIRIT checklist is provided in Additional file 1.

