This study has some limitations worth mentioning. First, there is no guarantee of comparable distribution of sociodemographic characteristics such as age and sex between intervention and control villages. Therefore, the true effect of the CHW interventions may be distorted by the natural progression of the diversity in the pattern of CVD risk factors. These variations will be minimized by using multi-level analysis with random effect models. Second, the diagnosis of hypertension using blood pressure readings taken on a single visit may overestimate the true prevalence of hypertension in the population. However, using an average of three blood pressure measurements (halfway and at the end of interview) will minimize the risk of white coat hypertension. Additionally, we will repeat the measurements on a separate occasion for individuals with elevated blood pressure to confirm hypertension. The risk of contamination of the intervention will be minimized by grouping and randomizing a group of three close villages to the same intervention arm. This will ensure that for each district, intervention villages will be together but far away (approximately 20 km) from control villages. There are still chances of interaction between people in the intervention and control villages. Other limitations of the study include unmeasured residual confounding and measurement bias for anthropometric measurements.

In conclusion, this study is the first randomized trial investigating the feasibility and effectiveness of CHW home-delivered interventions for the reduction of CVD risk factors in Tanzania. The findings of this study may be beneficial in influencing policy changes to enhance home delivery of health education, screening, and healthy lifestyle promotion interventions for the reduction of CVD risk factors in communities using CHWs.

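### Four bundles of three villages are randomised, but the 80% power is that of 12 independently allocated villages, so it assumes without saying so that villages in a bundle share no outcome variance

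*Protocol article*

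**What the plan says.** Randomization and blinding opens with "The unit of randomization will be the village", and Sample size estimation likewise describes a two-arm cluster trial that randomises villages. Randomization and blinding then describes something different. Six villages are drawn in each of two districts and sorted into two groups of three, using population size, type of health facility and distance between villages. After that, "One group of three villages from each district will be randomly assigned to intervention and another to control". The limitations paragraph of the Discussion confirms this, describing "grouping and randomizing a group of three close villages to the same intervention arm" as the protection against contamination.

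The intervention study is "calculated to provide an 80% power" and "to detect a ≥ 6.5 mmHg difference in mean SBP between the intervention and control villages at an alpha level of 5"%, with SD 15 mmHg, intracluster correlation (ICC) 0.03 and 20% attrition. The outcome of that calculation is: "The resulting sample size is 258 participants per arm of six villages". The test is two-sided: "For all analyses, a two-sided *p* value of ≤ 0.05 will considered statistically significant".

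**The concern.** Within a bundle, no village can receive a different arm from its neighbours. The randomised units are therefore four bundles, two per arm, and not twelve villages. The sample size text makes no allowance for correlation between villages in a bundle, or for having only four units.

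Two things are at stake for the primary outcome. If the analysis respects the level that was randomised, few degrees of freedom remain and power is far below 80%. If it treats villages as independent, its standard error is too small whenever neighbouring villages resemble one another in the outcome. The confidence interval is then too narrow, and a false positive is more likely than the nominal 5%.

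**Working it through.** **Inputs** (Sample size estimation; sidedness from Quantitative data): difference 6.5 mmHg, SD 15 mmHg, ICC 0.03, two-sided alpha 0.05, power 80%, attrition 20%, six villages and 258 participants per arm. That is 258/6 = 43 enrolled per village, 43 × 0.8 = 34.4 completers per village and 206.4 per arm. No baseline adjustment is applied, because the protocol gives no baseline/end-line correlation.

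**Step 1: reproduce the protocol's figure.** Take six independent villages per arm, so df = 2(6 − 1) = 10.
- Individually randomised size per arm: 2 × (2.228 + 0.879)² × 15² / 6.5² = 102.8.
- Completers per village: 102.8 × 0.97 / (6 − 102.8 × 0.03) = 34.2.
- Allowing for attrition: 34.2/0.8 = 42.8, rounded up to 43; 43 × 6 = 258 per arm.

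This matches exactly. The other usual formulas tried (normal quantiles with a design effect or with the number of clusters fixed, one extra cluster per arm, attrition as a 20% add-on) give 174 to 248.

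**Step 2: power as the protocol computes it.** Design effect = 1 + 33.4 × 0.03 = 2.002. SE = 15 × √(2 × 2.002/206.4) = 2.09 mmHg. Noncentrality = 6.5/2.09 = 3.11. Power from the noncentral t with 10 df is 80.0%.

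**Step 3: power at the level randomised, best case.** Suppose villages in a bundle share nothing. The SE stays at 2.09 and only the df change: four bundles in two arms give 2 df, and two district pairs give 1 df. Power is 41% and 19%. Reaching 80% with 2 df would need an SE of about 1.15 mmHg. With unlimited participants per village the SE cannot fall below 15 × √(2 × 0.03/6) = 1.50, which caps 2-df power at 62%.

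**Step 4: allow some of the 0.03 to be shared across a bundle.** The protocol gives no bundle-level correlation, so the share ρ_b is an assumption. The total within-village ICC is held at 0.03. Design effect = 2.002 + (103.2 − 34.4) × ρ_b, where 103.2 is the number of completers per bundle. The last column is the simulated rejection rate under no effect for a village-level t test with 10 df (200,000 or more runs).

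| ρ_b (of 0.03) | Design effect | SE, mmHg | Power, 2 df | Power, 1 df | Type I error, village test |
|---|---|---|---|---|---|
| 0 | 2.00 | 2.09 | 41% | 19% | 5% |
| 0.01 | 2.69 | 2.42 | 33% | 17% | 9% |
| 0.02 | 3.38 | 2.71 | 28% | 15% | 15% |
| 0.03 | 4.07 | 2.98 | 25% | 14% | 21% |

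In the same simulations the village-level test still rejects about 79% of the time under a true 6.5 mmHg effect. It looks adequately powered, but for any ρ_b above 0 it no longer holds its 5% error.

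**The case against.** The strongest reply is that the planned analysis is model-based and that villages are the natural clusters. This stands in part. If villages in a bundle share no variance, a village-level test keeps both 80% power and 5% error, and the drop from 80% to 41% in the best case comes wholly from the df. A reader might infer that the 80% power simply does not exist; the protocol does not support that. What can be said is that the 80% depends on an assumption that is neither stated nor defended, and that grouping villages by distance makes doubtful.

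Difference-in-differences also helps: stable area differences in blood pressure cancel, so what matters is shared variance in the change. The figures above use end-line variance and could shift. The protocol gives nothing from which to quantify this, and cancelling stable differences does not rule out shared change.

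Three further inferences should not be drawn.
- With 2 × 2 = 4 allocations, the smallest two-sided randomisation p-value is 2/4 = 0.5. That floor belongs to a permutation test, and the plan is a mixed-effects analysis.
- Arm is not shown to be confounded with health facility. The text lists the type of facility, not a shared facility, and does not say whether the criteria made villages alike within a group or balanced the two groups.
- The absence of a bundle term from the analysis section is not itself a fault. A condensed article may leave the model's levels to the SAP.

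**Conclusion.** The point holds in limited form. The protocol contradicts itself on the randomised unit: Sample size estimation and the opening of Randomization and blinding say village, while the allocation described there and in the Discussion is by bundle. The arithmetic behind 258 per arm is correct for 12 independently allocated villages, which is not the design described. At the level randomised, power is at most 41% (2 df) or 19% (1 df) on the protocol's inputs. It is 33% to 28% with 2 df if 0.01 to 0.02 of the ICC is shared within bundles, and a village-level test would then have a true type I error of about 9% to 15%. These figures assume no baseline adjustment, equal village sizes and the attrition stated; the bundle-level share is my assumption and not the protocol's.

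**What to change.** In Sample size estimation, Randomization and blinding and the limitations paragraph of the Discussion, name the bundle of three villages, stratified by district, as the randomised unit. Withdraw the 80% or restate power for that design, showing the range over assumed bundle-level correlation. State that a village-level analysis is valid only if bundle-level variance in the analysed outcome is negligible. Report a bundle-level analysis alongside it and accept that its power is low.

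The wording costs little. The real cost is acknowledging that a bundle-level result will probably be inconclusive; extra participants in the same 12 villages cannot cure that, given the 62% ceiling.

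One design alternative could be considered, since recruitment has not started: randomise well-separated villages individually, three to each arm within each district. With the same 516 participants and district as a stratum (9 df), power is about 79%. This gives up the deliberate grouping against contamination and needs enough mutually separated villages with active community health workers, which the protocol does not show to exist. It is an option and not a requirement of this point.
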